# A restaurant-based intervention to promote sales of healthy children’s menu items: the Kids’ Choice Restaurant Program cluster randomized trial

**DOI:** 10.1186/s12889-016-2892-5

**Published:** 2016-03-10

**Keywords:** Restaurant, Children, Healthy menu, Employee training

## Abstract

**Background:**

Away-from-home eating is an important dietary behavior with implications on diet quality. Thus, it is an important behavior to target to prevent and control childhood obesity and other chronic health conditions. Numerous studies have been conducted to improve children’s dietary intake at home, in early care and education, and in schools; however, few studies have sought to modify the restaurant food environment for children. This study adds to this body of research by describing the development and launch of an innovative intervention to promote sales of healthy children’s menu items in independent restaurants in Southern California, United States.

**Methods:**

This is a cluster randomized trial with eight pair-matched restaurants in San Diego, California. Restaurants were randomized to a menu-only versus menu-plus intervention condition. The menu-only intervention condition involves manager/owner collaboration on the addition of pre-determined healthy children’s menu items and kitchen manager/owner collaboration to prepare and plate these items and train kitchen staff. The menu-plus intervention condition involves more extensive manager/owner collaboration and kitchen staff training to select, prepare, and plate new healthy children’s menu items, and a healthy children’s menu campaign that includes marketing materials and server training to promote the items. The primary outcome is sales of healthy children’s menu items over an 18-week period. In addition, dining parties consisting of adults with children under 18 years of age are being observed unobtrusively while ordering and then interviewed throughout the 18-week study period to determine the impact of the intervention on ordering behaviors. Manager/owner interviews and restaurant audits provide additional evidence of impact on customers, employees, and the restaurant environment. Our process evaluation assesses dose delivered, dose received, and intervention fidelity.

**Discussion:**

Successful recruitment of the restaurants has been completed, providing evidence that the restaurant industry is open to working on the public health challenge of childhood obesity. Determining whether a restaurant intervention can promote sales of healthy children’s menu items will provide evidence for how to create environments that support the healthy choices needed to prevent and control obesity. Despite these strengths, collection of sales data that will allow comprehensive analysis of intervention effects remains a challenge.

**Trial registration:**

NCT02511938

## Background

Trends in eating food-away-from-home (FAFH) suggest children are eating more FAFH than ever before [1], with FAFH spending reaching a level nearly equal to food-for-home spending in 2014 [2]. Children’s daily caloric intake from FAFH increased from 23 to 34 % between 1977 and 2006, reflecting an increase from 447 to 702 calories (cal) from FAFH [1]. This is concerning given that multiple studies have found the nutritional quality of most restaurants’ children’s menu items do not meet nutritional standards [3–5]. As such, FAFH consumption has negative implications on children’s diet quality [6], with studies finding FAFH is associated with more consumption of energy, fat, added sugars, and sugar-sweetened beverages, and less consumption of milk, fiber, and fruits and vegetables (FVs) [7, 8]. In addition, at least weekly or more frequent consumption of FAFH is associated with obesity risk for United States (US) residents [9, 10] and elsewhere [11, 12], including in the present study community [13].

Responding to public health concerns, the National Restaurant Association started the Kids LiveWell program [14], an effort encouraging 42,000 predominantly chain restaurants to offer at least one full children’s meal (including side dish and drink) and one children’s menu item that meet nutritional standards. Despite this national effort, lacking are rigorous studies identifying the most effective strategies for promoting the sale of healthy children’s menu items in independent restaurants, which represent 66 % of all restaurants in the US [15]. Furthermore, restaurants offering ethnic foods are more likely to be independent [15], thus attracting segments of the population with the greatest health disparities (e.g., immigrants) [16, 17].

### Restaurant interventions

Restaurant interventions targeting children’s menu items are an innovative and potentially significant approach for improving the food environment [18], and consumption among dining parties [19]. For example, menu-labeling interventions have observed trends in decreasing calories purchased [20–22]. Other strategies also showed promise. In 13 outlets of one large chain restaurant, a menu modification intervention (i.e., 100 % of children’s meals included a healthy side dish and a healthy beverage) resulted in significantly fewer calories ordered by children who accepted the healthier default side and increased revenue for the restaurant chain [23]. More generally, a 2015 review of 27 restaurant interventions concluded that the only intervention strategies with some evidence are those that involve increasing the availability of healthy items on the menu and promoting these items through various modes or channels (e.g., point-of-purchase signage) [19]. However, most of the identified studies (20 of 27) did not meet criteria for inclusion in the review given weak study designs and lack of outcome data.

### Present study

Lacking are rigorously-designed studies evaluating methods for promoting healthy children’s menu items in independent restaurants. Most previous efforts have focused on chain restaurants [14]. The Kids’ Choice Restaurant Program (KCRP) is testing a multi-component intervention to promote the sales of healthy children’s menu items in independent restaurants in San Diego, CA. This paper describes the development of KCRP and presents baseline characteristics of the restaurants and managers/owners.

## Methods/Design

### Overview and study design

Consistent with CONSORT guidelines [24], KCRP is a cluster randomized trial with eight pair-matched independent restaurants randomized to a menu-only versus a menu-plus intervention condition. Outcome and impact evaluation activities are designed to determine whether the interventions result in sales of healthy children’s menu items and changes in ordering behavior among dining parties with children. Weekly sales data are collected from restaurant managers/owners for 18 weeks, including 4 weeks pre-intervention (baseline). Unobtrusive observations are attempted with approximately five dining parties with children every other week for 18 weeks in each restaurant to capture ordering behavior. Post-order and post-meal interviews with these same dining parties, as well as some unobserved dining parties, capture reported ordering and consumption behaviors. An extensive process evaluation protocol, including ongoing documentation by KCRP intervention staff, restaurant audits and manager/owner interviews, assesses key dimensions of implementation [25], including dose delivered, dose received, and intervention fidelity. Employees are recruited to participate in the restaurant training; however, the only evaluation activity they are involved in is assessment of the training. This study was conducted according to the guidelines laid down in the Declaration of Helsinki and all procedures involving human participants were approved by the Institutional Review Board of San Diego State University.

### Study foundation

The KCRP protocols are informed by formative research with restaurants in San Diego, CA, a pilot study in Imperial County, CA [26], the *Aventuras para Niños* restaurant intervention [27], input from members of the restaurant industry (see acknowledgements), as well as previous intervention research targeting changes to the food store environment [28–31]. The formative research study identified gaps in customer service, an issue important to restaurant managers/owners [32]. It confirmed the need to design materials that appeal to both parents and children given differences observed in ordering behaviors among older children. The pilot study confirmed the need to be prepared to take action with the restaurants immediately upon study enrollment versus waiting for the researchers to prepare their protocols, obtain institutional review board approval, etc. In other words, once they agreed, restaurant managers/owners were ready to begin study activities [26]. The *Aventuras para Niños* intervention identified the need to keep the intervention simple given high demands on manager/owner and restaurant staff time and effort [33]. Restaurant industry representatives informed the content and design of recruitment protocols and intervention strategies relevant to the restaurant managers/owners and customers involved in the present study. Our interventions are based on the integration of behavioral, organizational, and structural change theories [34–36], all of which fit under the Socio-Ecological Framework (SEF), which considers multiple sources of influence on health behaviors and health outcomes [37, 38]. SEF acknowledges the importance of organizational and structural models to inform intervention efforts to improve access to, and availability and promotion of, healthy foods and beverages [8, 39].

### Restaurant selection, setting, and intervention condition assignment

Restaurant eligibility included being a full-service restaurant (i.e., not quick service or buffet only); having a minimum of 20 tables; offering American or Latino food (i.e., the latter including but not limited to foods/beverages from Mexico, Puerto Rico, Cuba, Central and South America); and having sufficiently detailed receipts for coding purposes and/or the ability to provide detailed sales data. The first two criteria ensured that ordering would occur from among a large enough sample. Type of food was limited to minimize sources of variance such as sharing of meals, commonly observed in Italian and Chinese restaurants. Restaurant manager/owner eligibility criteria included being at least 21 years of age; having worked at least 20 hours per week for the participating restaurant for a minimum of 4 months; planning to continue working as restaurant manager/owner for the study duration; having decision-making authority in the restaurant; willingness to provide sales data to researchers; and not being employed at another participating restaurant.

Identification of permitted restaurants was conducted using February 2014 San Diego County Department of Environmental Health food permits, which yielded a list of 12,759 food outlets. After removing 5112 food establishments that were clearly not restaurants (e.g., lodging, grocery stores, convenience stores), and 1841 known national and regional chain restaurants (e.g., McDonalds), the list was reduced to 5806 outlets. This list was further reduced to a combined list of 1589 restaurants by targeting zip codes within a 5-mile radius of study offices and zip codes between 5 and 10 miles of study offices with a Latino population of at least 29 % using 2010 US Census data [40]. From this list, 92 American and Latino restaurants were identified as potentially eligible (see Fig. 1).

**Fig. 1 Fig1:**
[figure not shown]
Study design

Initial restaurant recruitment strategies involved a phone call or drop-in visit to schedule an in-person meeting with the restaurant manager/owner. If restaurant employees informed the KCRP recruiter that the restaurant manager/owner should be contacted first via email, an email with the introductory letter was sent. During the recruitment meeting with the manager/owner, the KCRP recruiter reviewed study requirements and gave the manager/owner a study fact sheet with testimonials from managers/owners who participated in the pilot study and answers to frequently-asked questions. In addition to learning more about the study, the manager/owner was told his/her restaurant would receive $300 for participating, the manager/owner would receive $20 for each of two interviews completed, and wait staff and customers would receive $10 per shift and $5, respectively, the former for allowing KCRP evaluation staff to shadow the wait staff and the latter for completing the interviews. If the manager/owner was interested, the KCRP recruiter completed eligibility screeners for both the restaurant and the manager/owner. If eligibility was met and the manager/owner agreed, the two parties signed a letter of agreement and confidential disclosure agreement. The manager/owner also signed an informed consent form for the interviews. Restaurants were pair-matched on availability of a children’s menu (yes or no) and with one exception, on size (small-to-medium or medium-to-large based on number of tables). The exception involved one set of pair-matched restaurants both without a child menu but of different sizes. Once a pair was identified, the project biostatistician randomly assigned each restaurant to either the menu-only or menu-plus intervention condition and the intervention planning and development phase for the pair commenced. KCRP evaluation staff blinded to intervention condition assignment completed baseline measures.

### Intervention conditions

In both the menu-only and menu-plus intervention conditions, the children’s menu intervention is implemented over a 10-week period. This occurs after an initial start-up period of about 6 weeks during which KCRP intervention staff work with the restaurant manager/owner to decide upon the various intervention components. In both intervention conditions, restaurants are asked to consider children’s menu items that fit their current inventory to minimize the number of new ingredients needed. Restaurants with an existing children’s menu are encouraged but not required to remove existing menu items from their offerings.

#### Menu-only intervention condition

Restaurants randomly assigned to the menu-only intervention condition are provided a standard set of healthy children’s menu items to include in their offerings on a new color-printed and laminated children’s menu provided by the study (see Table 1). All meals meet nutritional standards that reduce calories, fat and sugar compared with traditional children’s menu items. To do this, the following strategies are used: (a) decreasing portion sizes of existing and proposed menu items, an important though challenging target for change [41]; (b) adding fruit and vegetable side dishes to the menu, sometimes with serving sauces, which is one method for overcoming food neophobias that children may have to new foods and beverages [42]; and (c) establishing healthy side dishes as the default, which may reduce calorie intake by up to 170 cal [23]. Previous research has shown small changes in default foods can improve the nutritional value of foods promoted to children, especially if an indulgence is maintained (e.g., smaller sized french-fry portion plus apple slices) [43]. Children have neutral or positive attitudes toward these changes [4]. Thus, consistent with the concept of behavioral economics to automatize the selection of healthier versus less healthy items [23], and because of the importance of having choices and being flexible [32], our children’s meals include a healthy side dish as a default and sometimes a healthy beverage (i.e., 1 % or skim milk; 100 % orange or apple juice). Importantly, only healthy beverages are included on the new children’s menus; however, per owner/manager preferences, substituting a previously available side dish or beverage is possible. To finalize the menus, decisions are made about their pricing and plating. Given parent and child preferences for “all-in-one” pricing (e.g., main dish, side and beverage) and pricing that is similar to unhealthy menu items [42], managers/owners are encouraged to set an “all-in-one” price and to be consistent with the pricing of other children’s menu items. How foods are presented (e.g., food appearance and portion size) [5, 44, 45] influences choice, thus it is suggested to use smaller plates to retain a pleasing ratio of food to “white-space” [46].

**Table 1 Tab1:** Intervention components and associated process evaluation measures for menu-only and menu-plus conditions

	Planned dose	Process evaluation
Menu-only		
New healthy children’s menu	Five standard healthy children’s meals that meet the following criteria in combination with side dish and beverage offerings: no more than 600 cal; no more than 50 % calories from fat; no fried foods; child-appropriate portion sizes; fruit or vegetable side dishes; healthy beverages (1 % or nonfat/skim milk and/or 100 % fruit juice [e.g., orange or apple])	# of main dishes implemented # of side dishes implemented # of healthy beverages implemented Mean calories per meal combination available $ spent on kitchen supplies to prepare new items Retention of existing children’s menu items Mean amount of time spent on kitchen manager meeting
	Kitchen manager meeting to prepare new recipes	
Menu plus		
New healthy children’s menu	Same as menu-only with more flexibility in terms of choices offered	Same as menu-only
Marketing campaign	One banner	% (n) of banners installed and retained at each weekly visit; placement of banners % (n) of table tents installed and retained at each weekly visit # of customers observed looking at KCRP materials Impact of design elements on sales
	Table tents (quantity based on number of tables)	
Trainings	All servers, bus-persons and hosts/hostesses invited to receive 15-min introductory training	Median (range) and % of servers, bus-persons and hosts/hostesses who received 15-min introductory training % of those attending introductory training who also received advanced training % of observations in which server was observed prompting use of KCRP materials # of pocket guides distributed at trainings % of kitchen employees who received kitchen staff training % of training content that was completely covered for all trainings
	At least 50 % of servers, bus-persons and hosts/hostesses who attended introductory training invited to attend 15-min advanced training	
	All kitchen staff invited to receive 15-min kitchen staff training	

Following selection of menu items, a KCRP intervention staff member meets with the kitchen manager who is responsible for training the kitchen staff to adopt the new menu items for at least 10 weeks. Kitchen managers/chefs work with a KCRP intervention staff member on the preparation and plating of the new children’s menu items during one meeting lasting between 45 and 90 minutes (min). A key focus of this meeting is on food portion sizing for children. Kitchen managers/chefs then train the kitchen staff on the preparation of the new items.

The healthy children’s menu in the menu-only intervention condition includes five main dishes, at least three side dishes and two beverages (see Fig. 2). The nutritional quality of each meal combination is evaluated against current nutritional standards [14, 47, 48]. Meals, including a healthy side dish and a healthy beverage, range from 142 to 601 cal. Main dish items are between 37 and 366 cal. Since restaurants are not required to remove existing children’s menu items or modify any aspect of adult menu items, children could substitute existing side dishes and beverages when ordering a new children’s meal. New children’s menus are printed with the restaurant and project logos and include the price and what the price includes (e.g., with or without a beverage). However, unlike the menu-plus intervention condition as described below, meal names are presented in a randomly ordered list. Printed menus are distributed to dining parties consistent with restaurant practices.

**Fig. 2 Fig2:**
[figure not shown]
New healthy children’s menu for menu-only condition

#### Menu-plus intervention condition

Similar to a previous study [49], restaurants randomized to the menu-plus intervention condition are engaged in a more collaborative process of: (a) identifying healthy children’s menu items that may fit better with their existing adult and children’s menus (if available); (b) implementing a healthy children’s menu campaign that includes a printed children’s menu with copy and design elements that influence ordering behavior [50], a banner and table tents; and (c) kitchen staff and server training to prepare and promote the new healthy children’s menu items (see Table 1). Regarding the menu items, to maximize the sales of new children’s menu items, decisions about what items to include, their recipes, prices, etc., are made over three to four meetings with the restaurant manager/owner. It is important to get manager/owner buy-in to maximize implementation fidelity [51]. Regarding the campaign, the menus use copy and design elements that have been shown to capture consumers’ attention, including fun names and descriptions of the new menu items, placement of new menu items in specific locations on the menu, and boxing menu items and including pictures to draw attention to them (see Fig. 3) [50]. In short, the menu-plus intervention condition involves social and structural changes in the restaurants, with activities directed at the managers/owners, employees, and customers. Research-supported intervention activities geared toward development of the menus and campaign occur over several weeks immediately prior to the 10-week customer-directed activities.

**Fig. 3 Fig3:**
[figure not shown]
New healthy children’s menu for menu-plus condition

#### Healthy menu campaign

The goal is to change ordering behavior through a healthy menu campaign. Outside banners are used to draw dining parties with children into the restaurants. Table tents and banners are used to promote the menu items, similar to previous research [49]. The materials are designed to appeal to both children and adults given the increased autonomy children exhibit in restaurant ordering, compared with other food-related decisions [42].

#### Employee trainings

In addition to the kitchen manager meetings, in the menu-plus intervention condition, kitchen staff receive a 15-min training introducing the KCRP project and the new children’s menu items in their proper portion and plating arrangements. Servers, bus-persons and hosts/hostesses also receive one 15-min introductory training, and a subset of servers, bus-persons, and hosts/hostesses participate in a second 15-min training a few weeks later. Using a script and slide presentation, KCRP intervention staff train the employees on the following topics: customer service and suggestive selling, interacting with dining parties with children, and promoting the new children’s menu items. Server training was identified as an important strategy for creating a stress-free environment, a factor identified as important to parents with young children when selecting a restaurant [42, 52]. These trainings occur during the development phase and prior to implementation of the new children’s menu and the healthy menu campaign. Optimal delivery of the trainings occurs in small groups; however, they can be delivered one-on-one. Trainings include opportunities for role playing and skill practice consistent with behavioral modification principles [53]. At the end of the introductory training session, employees are given a pocket guide to remind them of the key points of the training and provided strategies.

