### Intervention implementation

The interventions are initiated once all baseline data are collected, menu items are selected, menus are finalized, and trainings are completed; for each pair-matched restaurant, interventions start on the same day. After the new children’s menus are introduced (along with the healthy menu campaign in the menu-plus intervention condition), a KCRP intervention staff member conducts on-site support visits with each restaurant to monitor implementation and help restaurant managers/owners address any issues that may arise with the new children’s menus. These visits occur three times over the 10-week intervention for menu-only restaurants and weekly for menu-plus restaurants. Support visits consist of informal meetings lasting approximately 15 min that are guided by a set of open-ended questions and allow for discussion of any outstanding issues that need to be addressed. A KCRP intervention staff member monitors implementation to maximize implementation fidelity, addressing concerns with the manager/owner either immediately or soon after they are identified.

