### Evaluation

#### Overview

A mixed-methods approach is used to evaluate the intervention on sales of healthy children’s menu items over an 18-week period, including during the 4-week baseline period. Primary outcomes are gross sales of healthy children’s menu items and units sold. Observations and interviews with a convenience sample of dining parties with children below the age of 18 years will determine changes in ordering behavior. Manager/owner interviews conducted during the baseline period and during the final 4 weeks of the 18-week data collection period (herein referred to as post-intervention period), and restaurant audits at baseline, mid-point of intervention and post-intervention periods will provide evidence of intervention impact on the manager/owner and restaurant environment. Our process evaluation includes an additional manager/owner interview once intervention activities are completed (i.e., exit interview). KCRP intervention staff visit the restaurants to capture implementation, dose delivered, dose received, and fidelity, and manager/owner and customer satisfaction with the intervention (see Table 1).

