## Discussion

From among the 92 potentially eligible restaurants, 32 were ineligible prior to approaching the manager/owner for not being a full-service restaurant, having too few tables, or not having the capability to provide sales data. From the remaining 57 restaurants, 10 never responded to any recruitment attempts and six were never approached due to completion of recruitment. Forty-one restaurants were approached in-person for participation; nine were ineligible, 18 refused to participate, six never provided a final decision, and eight agreed (see Fig. 1). Among the reasons given for participating, managers/owners noted that they were interested in providing healthier items for children. Among reasons for refusing, managers/owners said they were too busy or not interested, their restaurants were undergoing major changes during the upcoming months, or the timing of the study necessitated more extensive management involvement than they could provide during the peak tourist season. However, other managers/owners reported they were not interested in “telling customers how to eat” or did not want to change their existing menus.

Restaurants are pair-matched at recruitment to ensure equivalency across characteristics randomized to intervention conditions (e.g., presence of a children’s menu). Thus, once a restaurant is recruited, a second restaurant from the list is recruited with similar characteristics. One restaurant is randomly assigned to the menu-only intervention condition and the other to the menu-plus intervention condition. Baseline assessments take place during the 4 weeks prior to the introduction of the new children’s menus and are conducted by KCRP evaluation staff blind to treatment condition.

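### Part of the 4-week baseline probably follows server training in menu-plus only, so baseline existing-item sales, total sales and ordering behaviour may already include a training effect; primary sales of the new items are unaffected

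*Protocol article*

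**What the plan says.** Under the section on restaurant selection and condition assignment, each pair is randomized and its planning and development phase then begins. Under Intervention conditions, "the children’s menu intervention is implemented over a 10-week period", and "This occurs after an initial start-up period of about 6 weeks". The Menu-plus section puts that arm's development work directly before the 10 weeks.

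Baseline is fixed in the Discussion: "Baseline assessments take place during the 4 weeks prior to the introduction of the new children’s menus". The Evaluation overview adds a post-intervention period, placed "during the final 4 weeks of the 18-week data collection period".

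Under Employee trainings, menu-plus servers, bus-persons and hosts receive an introductory session. Some of them then "participate in a second 15-min training a few weeks later". The topics are customer service, suggestive selling, dealing with families, and promoting the new items. On timing: "These trainings occur during the development phase and prior to implementation of the new children’s menu and the healthy menu campaign". Table 1 lists no server training for menu-only.

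Under Intervention implementation: "The interventions are initiated once all baseline data are collected, menu items are selected, menus are finalized, and trainings are completed". This makes baseline and training joint conditions for launch but does not say which comes first.

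The primary outcomes are dollar and unit sales of healthy children's items. Sales of existing children's items and total food and beverage sales are also tracked from baseline. So are biweekly dining-party observations, which record whether servers engage with children and recommend children's-menu items.

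**The concern.** A baseline serves as a reference only if neither arm has yet been treated. Here allocation precedes baseline, and one arm's servers are trained in the same weeks. Suggestive selling and attention to families can be practised on the old menu, and both are close to what the observers score. If trained servers already behave differently during baseline, the menu-plus reference level moves toward its intervention level and the measured change shrinks.

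There is a second route. Under Planned analyses, characteristics that differ significantly between conditions enter the mixed model as covariates. If a baseline outcome value shifted by training were selected that way, adjustment would remove part of the effect being estimated.

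**Working it through.** **The plan's own window.** 4 baseline + 10 intervention + 4 post-intervention = 18 weeks, as stated. Five parties at each of 9 biweekly visits = 45 per restaurant, also as stated. The 18 weeks are fully used, so no gap separates baseline from launch.

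**Overlap with start-up.** Set launch at week 0. Start-up runs from about week −6 to 0 and baseline from week −4 to 0. The overlap is 0 − (−4) = 4 of 4 baseline weeks. If menu-plus development took only 2 or 3 weeks, the overlap would be 2 or 3 of 4. If start-up instead ended before baseline began, the trainings would precede baseline and all 4 weeks would follow them.

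**Baseline weeks after the first server session.** Let the two sessions be g weeks apart. The second falls at or before week 0, so the first falls at or before week −g, and at least min(4, g) baseline weeks follow it. The article gives no value for g, so a range is shown.

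| Gap g (weeks, assumed) | Minimum baseline weeks after first session | Minimum share | Maximum share |
|---|---|---|---|
| 0 | 0 | 0% | 100% |
| 1 | 1 | 25% | 100% |
| 2 | 2 | 50% | 100% |
| 3 | 3 | 75% | 100% |
| 4 | 4 | 100% | 100% |

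Only a gap near zero, with all training just before launch, allows a baseline almost free of training. That does not fit sessions described as weeks apart.

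**Which outcomes are reached.** Let f be the exposed share of baseline. Let ρ be the effect of training alone, before launch, as a share of the full effect. A baseline-referenced change then recovers 1 − fρ of the effect.

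- Sales of new healthy items: nothing is on sale before launch, so ρ = 0 at baseline and 1.00 is recovered whatever f is.
- Outcomes measurable at baseline: ρ is unknown. For illustration only, f = 0.5 and ρ = 0.25 gives 1 − 0.125 = 0.875; f = 1 and ρ = 0.5 gives 1 − 0.5 = 0.50.

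**Baseline observations available.** Four weeks of biweekly visits at about five parties is 2 × 5 = about 10 parties per restaurant. With 50% to 100% of them after training, 5 to 0 remain in each menu-plus restaurant.

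**The case against.** The strongest reply is that the primary outcome escapes. The article says funding does not allow existing children's items to be rated for nutritional quality, so the healthy items are in effect the new ones. Their baseline sales are zero in both arms by construction. This stands. A reader might infer from the overlap that the main result is biased, and the article does not support that.

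Next, no passage dates the trainings against the baseline weeks, and every duration is approximate. This stands too: a baseline already treated in one arm is a strong inference and not a stated fact, and exposure may be partial. A condensed article may leave the training calendar to the full protocol. But the intervals it does print leave little room for a baseline free of training, and its launch rule does not protect one.

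Third, the exposure before launch is weak: 15-minute sessions, with no new menu, banner or table tent in place, and one topic about items that cannot yet be ordered. This limits the likely size, but the general selling and service skills remain usable.

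Fourth, Planned analyses names a mixed model with condition and sales over time. It specifies neither a change score nor adjustment for the baseline outcome, and significance is a high bar with four restaurants per arm. Adjusting away the effect is therefore a possible consequence of the covariate rule and not a planned step.

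Finally, a reader might infer that baseline blinding fails because observers work beside trained servers. The article states that baseline staff are blinded and has intervention staff deliver the training. Nothing in it shows unblinding, so that inference is speculative.

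**Conclusion.** The concern holds for outcomes measured from baseline: existing children's-item sales, total sales, and observed or reported server and ordering behaviour. It does not hold for primary sales of the new items, on the reading that healthy items are the new ones.

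As scheduled, all 4 baseline weeks lie within a 6-week start-up, and at least 2 of 4 follow the first menu-plus server session if the sessions are 2 weeks apart. This rests on both sessions preceding launch, as the article says, and on an assumed gap.

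If training acts in the same direction as the full intervention, the change in these outcomes would be understated. The amount cannot be computed, because the effect of training before launch is not given. Any specific percentage, including the illustrations above, depends on that assumption. This is a correctable sequencing flaw that does not invalidate the trial.

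**What to change.** 1. State the order of baseline and server training. For pairs not yet launched, close the baseline window before the first menu-plus server session.
2. For pairs already under way, request the 4 sales weeks before start-up from both restaurants of the pair, and use them as baseline for existing-item and total sales.
3. Record training dates; the sign-in sheets already kept are a natural place. Label dining-party observations after the pair's first training date as a separate run-in period, in both restaurants so that the comparison stays symmetric.
4. Where too few pre-training observations remain, keep the run-in observations and report a sensitivity analysis with and without them. Outright exclusion could leave 0 to 5 of about 10 baseline parties in a menu-plus restaurant.
5. Exclude from the covariate rule any outcome value measured after training began.

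The cost is a slightly longer lead-in for later pairs, one extra sales request per restaurant in pairs under way, and fewer clean baseline observations in those pairs. The sales request is not free: the abstract names sales-data collection as a continuing challenge, although restaurants were selected for detailed receipts or the ability to supply such data. The content of the intervention does not change.
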